#### Sample Size Justification and Power Analysis

Given that the goal of this study is not to test a specific hypothesis, but rather to iterate over an entire data set to develop higher-level multivariate models, sample size and power analysis are less relevant for our study design. However, multiple strategies will be included to ensure data sufficiency. Collecting 12 weeks of daily self-reports and continuous smartwatch-derived features for up to 500 participants will enable multiresolution feature engineering while preserving participant-level separation during model evaluation (nested cross-validation, train-validate-test splits by participant). Outcome-event counts will be monitored to reduce overfitting risk. We expect to include approximately 35 Apple Watch–derived features (eg, physiological and physical function and sleep) in our primary model, alongside demographics (eg, age, sex, social determinants of health), pain-related features (eg, pain diagnoses, medical history), and task-based performance metrics (TSST-OL, 30s-STS) in secondary models. Model complexity controls, such as regularization, feature reduction, and early stopping, will be incorporated as needed. Furthermore, our sample of up to 500 participants will far exceed those found in comparable studies [20,44]. Achieving 80% of the target recruitment (ie, 400 participants) is also sufficient based on outcome-event counts and comparable studies.

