**Figure 2 figure2:**
[figure not shown]
Timeline of TRAC-Pain (Targeted Real-Time Assessment of Chronic Pain) study. The study begins with surveys completed at baseline. Participants wear a smartwatch for 12 weeks and complete "daily check-in" surveys about their pain experience. At discharge, participants are invited to complete a modified online Trier Social Stress Test and 30-second sit-to-stand task (30s STS). Finally, implementation outcomes are assessed through a semistructured exit interview to guide future applications. HEAL CDE: Helping End Addiction Long Term Common Data Elements; SDOH: Social Determinants of Health.

**Table 1 table1:** Timeline of tests and measures for the Targeted Real-Time Assessment of Chronic Pain (TRAC-Pain) study.

Domain and tests/measures					Time points administered						
					Baseline		Daily		Continuous		Discharge

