	**Physiological response to stress task**										
		Self-report distress metrics, Apple Health Kit metrics collected during TSST-OL^p^									✔

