	**Functional Task Performance**										
		Number of sit-to-stand-stand repetitions completed, joint kinematics, Apple Health Kit metrics									✔

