The participants are instructed to wear the Apple Watch for at least 18 hours per day during the 12-week observation period. Apple Health Kit data are collected, uploaded, and stored through the third-party digital health and research platform. Metrics of interest include those related to respiratory function (eg, respiratory rate), heart activity (eg, heart rate, heart rate variability), physical activity (eg, steps, bouts of activity, standing time), sleep (eg, in-bed time, sleep phases), and mobility (eg, gait speed, walking asymmetry, step length) (Table 1). Survey completion rate and adherence to required watch wear times are monitored by the study team. Participants receive notifications from the study team to encourage high levels of adherence based on completion standards selected a priori (eg, number of daily check-ins completed each week and daily and nightly hours of wear). Participants receive weekly monetary incentives for completing each component of the study, with up to US $210 total. Those who do not meet adherence standards may not be eligible to receive a given week’s compensation. Furthermore, those consistently not meeting standards within the first few weeks of the study may be withdrawn in an effort to allocate research team time to adherent participants and prevent excessive amounts of missing data. At the end of the 12-week observation period, the participants complete an additional battery of discharge surveys, once again deployed through the third-party app (Table 1). They also complete a series of task-based measures prior to study discharge.

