### Task-Based Measures (Secondary)

#### Overview

The participants complete an additional stress task and a functional task to capture physiological responses to standardized challenges. These tasks are collected on a subset of the study cohort to examine responses to acute stressors. Although not required for the development of the initial biosignature, physiological responses and performance metrics related to these standardized challenge paradigms may improve the sensitivity of the biosignature in future iterations. Additionally, the results will provide unique insight into the pain experience by allowing for a standardized comparison across participants, supporting future hypothesis generation.

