### Analysis Plan

#### Outcome Measures

A digital biosignature will be developed to enable the detection of a change in pain status. The primary outcome used to validate the biosignature (ground truth) will be the participant’s self-reported onset of a pain flare. Additional models will be explored to predict secondary outcomes such as a clinically relevant change in pain interference, namely, 2 units on the Pain, Enjoyment of Life, and General Activity (PEG 3-item) scale or the onset of pain flares lasting for more than 2 days only. To improve pain flare prediction, participants may be stratified by demographic features known to impact the pain experience, and models may be adjusted using partial correlation. Accounting for individual factors may be particularly relevant when considering differences in digital access and literacy among participants residing across diverse geographic locations.

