#### Data Reduction

Raw physiological signals (eg, heart activity, step counts, sleep stages) will be synchronized across modalities and aligned to a common timeline while preserving native sampling frequencies. To capture information across temporal scales, features will be engineered using a *multiresolution aggregation strategy*. For each signal, summary statistics will be computed over short windows (seconds to minutes) and further aggregated into intermediate (hourly) and daily summaries. All features derived at finer resolutions will be consolidated into a single daily feature vector, enabling the integration of short-term variability and longer-term physiological trends. The model prediction target and evaluation will be defined at a chosen time scale (eg, daily). Any windowing will only use past data relative to the prediction time to avoid leakage.

In addition to static summaries, *dynamic features* will be generated to characterize within-day temporal structure and behavior. These may include acceleration-based metrics (eg, mean acceleration), measures of temporal change (eg, slopes and rates of change), and circadian rhythm features. Complexity metrics (eg, entropy-based measures) may also be included to quantify signal regularity.

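### Stress-test and sit-to-stand metrics are measured once, at discharge, yet are planned as inputs to secondary models whose named targets arise in the preceding 12 weeks

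*Protocol article*

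**What the plan says.** **Planned use.** Sample Size Justification and Power Analysis describes a primary model with about 35 Apple Watch features. It then expects demographics, pain-related features and "task-based performance metrics (TSST-OL, 30s-STS) in secondary models".

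**Timing of the tasks.** The Figure 2 legend states: "At discharge, participants are invited to complete a modified online Trier Social Stress Test and 30-second sit-to-stand task". Smartwatch Metrics (Primary), having described the end of the 12-week observation period and the discharge surveys, adds: "They also complete a series of task-based measures prior to study discharge". In Table 1 the stress-task row ("Self-report distress metrics, Apple Health Kit metrics collected during TSST-OL") and the functional-task row ("Number of sit-to-stand-stand repetitions completed, joint kinematics, Apple Health Kit metrics") are each ticked once, under Discharge. Neither has a baseline tick.

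**Who does them.** The overview of Task-Based Measures (Secondary) says: "These tasks are collected on a subset of the study cohort to examine responses to acute stressors". It also says that the first biosignature does not need the tasks and that they might sharpen later versions of it.

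**Targets.** Outcome Measures makes the participant's "self-reported onset of a pain flare" the primary ground truth. It names two secondary targets: a 2-unit change on the PEG, and onset of flares lasting more than 2 days.

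**Leakage rule.** Data Reduction states: "Any windowing will only use past data relative to the prediction time to avoid leakage".

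**The concern.** A predictor has to be available before the thing it predicts. Here the challenge-task scores come after the flares and PEG changes that the article names as modelling targets. Flare burden over 12 weeks could itself alter how many sit-to-stand repetitions a participant manages, or how strongly the participant reacts to a stress test; the 30s-STS section itself describes the systems tested as ones that chronic pain may affect. A secondary model that improves when these scores are added might therefore be reading the past and not anticipating the future.

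At stake is the inference that challenge tasks improve flare prediction. That inference would bear directly on whether they are built into the later versions of the biosignature that the task overview has in mind.

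**Working it through.** No power, alpha or sample-size figure is involved, so the check is one of timing, followed by a simulation to see what the data could show.

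**1. When the predictor is measured.** The Figure 2 legend, both Table 1 rows and the Smartwatch Metrics text agree: once, at the end of the 12 weeks. No section gives a baseline or mid-study task measurement.

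**2. When the targets are measured.** Daily check-ins, including the flare question and the PEG, run for the whole 12 weeks: 12 × 7 = 84 days per participant. At full enrolment and completion that is 500 × 84 = 42,000 participant-days. The PEG is also taken at baseline and discharge. No outcome window after the tasks is described.

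**3. The order.** Essentially all 84 days precede the task score. This holds for each of the three named targets, so it does not matter which of them a secondary model uses.

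**4. Whether the planned safeguards catch it.** Participant-level splits and nested cross-validation stop information passing between people. The problem here lies within a person: a held-out participant's discharge score still post-dates that participant's own flares. SHAP could rank such a score as a key feature. The Phase 2 description mentions no task measurement, so as described it would not test the finding.

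**5. Whether the discharge data could separate cause from consequence.** Simulation of 400 × 84 = 33,600 person-days with one constant score per person. The document gives none of the following, so they are assumptions: daily flare rate 10% for the median person; between-person SD of the flare log-odds 0.5, 1.0 or 1.5; correlation r of 0.3 to 0.5. Two kinds of score were compared by AUROC over person-days: one built only from the realised flare count (a pure consequence), and one fixed before any flare and correlated to the same degree with the person's underlying flare propensity (a genuine prior trait).

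| SD of log-odds | Pure consequence, r 0.3 to 0.5 | Prior trait, r 0.3 to 0.5 |
|---|---|---|
| 0.5 | 0.55–0.58 | 0.54–0.57 |
| 1.0 | 0.58–0.64 | 0.58–0.63 |
| 1.5 | 0.61–0.68 | 0.60–0.66 |

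With r = 0 the AUROC is 0.50. The two columns differ by no more than about 0.02, and a 20% flare rate gives the same picture. The AUROC reflects between-person correlation and is almost blind to the direction of time.

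**The case against.** **The text says secondary models, not flare models.** Correct. The sentence sits in a sample-size paragraph and names no target for them, and the task overview gives the tasks other uses, such as comparing participants and generating hypotheses. But every target the article does name falls within the 12 weeks. The sentence therefore needs a limit that it does not have.

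**The past-data rule governs windows on sensor signals.** Also correct. A reader might infer a direct breach of that rule; the wording does not support this, because a single task score is not a windowed signal. What stands is a conflict with the rule's stated purpose, avoiding leakage.

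**A task score may be a stable trait.** This could be defended if it were stated. The article does not state it, and one discharge measurement cannot establish it.

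**The consequence is limited.** This stands. The primary model uses watch features only, the tasks are labelled secondary and not needed for the initial biosignature, and there is no formal hypothesis test. A reader might infer that the biosignature itself is contaminated; nothing in the document supports that.

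**No comparison of models with and without the tasks is planned.** The article states none, so it cannot be faulted for comparing different samples. The subset becomes a problem only if such a comparison is made.

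**Conclusion.** The point holds for the secondary models. As written, the plan allows measurements taken at discharge to enter as inputs to models of outcomes collected over the preceding 84 days, and none of its validation steps would expose the reversed order. The article also places predictive use of the tasks in two settings, later versions of the biosignature and this study's secondary models, and these need reconciling.

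This should be fixed, but it does not threaten the primary result. The size of any distortion cannot be estimated from the document. It would be tempting to read the simulated AUROCs of about 0.54 to 0.68 as the spurious performance to expect. They do not show that: a genuine prior trait gives nearly the same values, and they describe the score alone, not its gain over a model already holding about 35 watch features. They show only that discharge data cannot tell a consequence of flares from a predictor of them.

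The conclusion assumes that the secondary models address the targets named under Outcome Measures and that no earlier task measurement exists. The article mentions none.

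**What to change.** Reword the sentence in Sample Size Justification and Power Analysis so that TSST-OL and 30s-STS metrics are not used as predictors of outcomes in the 12 weeks before they were measured. In particular:

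- Analyse them as discharge outcomes, or as person-level associations with 12-week flare burden and watch features, and label the results as association, not prediction.
- Keep predictive use for scores obtained before the outcomes being predicted. This agrees with the task overview, which looks to later versions of the biosignature.
- If models with and without the task metrics are compared, fit both in the same participants, namely those who completed the tasks.

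**Cost.** One sentence changes. A secondary Phase 1 prediction model is lost or relabelled; no data collection is lost. With 190 participants enrolled at 15 December 2025 and analysis ongoing, the change is best made before these models are fitted.

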## Results

This study was funded in September 2024, with data collection beginning in March 2025. As of December 15, 2025, 190 participants have been enrolled, with data collection and analysis ongoing.

## Discussion

### Expected Findings

The purpose of this study is to develop a digital biosignature of the pain experience in youth and adolescents with chronic MSK pain. Self-report measures are the current gold standard for monitoring the pain experience and informing clinical decision-making. The purpose of developing a digital biosignature is to overcome the limitations of self-report, specifically the tendency to represent a single point in time and its inherent vulnerability to recall bias. A digital biosignature will provide real-time, objective measures of the pain experience through a holistic, multisystem lens.

This study is expected to result in several clinical benefits. First, the development and validation of digital clinical end points facilitates more robust assessment of novel therapeutics and treatment paradigms for youth with chronic MSK pain. The precise monitoring of treatment response would enhance the rigor and effectiveness of clinical trial design, leading to improved treatments, especially for those refractory to existing therapies. Second, a digital biosignature will give clinicians a deeper understanding of their patients’ individual pain experience through real-time, longitudinal monitoring of symptom fluctuations. These insights will enhance clinical decision-making and support a shift toward individually tailored interventions. Real-time tracking will also facilitate expedited shifts in a prescribed treatment plan, saving time and resources in helping patients to find the best treatment option for their specific pain presentation. Additionally, an objective biosignature may improve patients’ pain experience and interactions with clinicians by reducing the need to repeatedly recount severe pain events, an act that itself may be distressing. Finally, not only will a digital biosignature inform clinical practice, but it will also empower patients to have more control over their symptoms. Specifically, Phase 2 addresses this last point through enhanced “wellness alerts” for improved self-efficacy in living with chronic pain.

### Future Directions (Phase 2)

To further the impact of the digital biosignature that will be developed in this study, we expect to conduct a second phase of the study. The goals of Phase 2 are twofold: (1) assess clinical validation of the digital biosignature in a novel sample and (2) evaluate the accuracy of a predictive “wellness alert” system.

Phase 2 includes recruitment of a novel cohort of up to 400 youth with MSK pain. Recruitment criteria will mirror those described in this study. To ensure relevance of the digital biosignature for a representative set of adolescents, this phase will have a particular focus on recruitment of youth experiencing health disparities (eg, rural youth with limited access to tertiary pain clinics and racial and ethnic minorities). Once again, a multipronged recruitment strategy will be implemented as described in this study. Stanford Medicine’s Trial Innovation Network will provide additional support for the recruitment of youth and adolescents experiencing health disparities. Participants will use an iPhone and Apple Watch for 12 weeks to monitor physiological, sleep, and physical activity data. Devices will be provided as needed. Metrics such as AUROC, AUPRC, *F*_1_-score, positive predictive value, and negative predictive value will be used in this study phase for prospective validation of the digital biosignature. As in Phase 1, we expect that participants’ self-reported pain flare onset will be used as the primary outcome to which the digital biosignature is compared.

Participants enrolled in Phase 2 also have the opportunity to receive enhanced “wellness alerts,” which would be triggered by a deterioration in the pain experience as detected through abnormal smartwatch readings. The goal of these “wellness alerts” is to prompt users toward proactive self-management strategies (eg, pacing, sleep hygiene) in an effort to prevent or reduce the severity of the predicted pain flare. Patient and advocacy partners recommended positive framing of these “wellness alerts” (ie, opportunities for enhanced wellness strategies) as opposed to “pain flare predictions,” which may be negatively interpreted and lead to increased anxiety and hypervigilance. The accuracy of the enhanced “wellness alerts” will be assessed via comparison to self-reported pain flare onset through measures of accuracy, precision, and true positive and false negative rates. This “wellness alert” system is expected to empower patients by reducing feelings of helplessness surrounding unpredictable fluctuations in pain status. In addition, the alerts may serve as an additional tool to promote pain-related self-efficacy, which may serve as a protective factor in youth with chronic pain [45].

### Access and Dissemination

Although this study uses the Apple Smartwatch as a wearable technology of choice, the algorithms developed can be expanded across multiple monitoring options to promote broader dissemination and encourage improved access to study innovations. This study will introduce opportunities for open-access analysis tools that can be deployed across different wearable devices for improved dissemination. Furthermore, the identification of key physiological features may suggest that simpler, more economical fitness technologies (eg, pedometer or heart rate monitor chest strap) are sufficient for characterizing the pain experience in this population.

### Conclusions

The TRAC-Pain study leverages the widespread adoption of consumer wearables to overcome limitations of self-report as the current gold standard for monitoring the pain experience in youth with chronic MSK pain. This study is unique in its multipronged recruitment strategy and intentional collaboration with patient and advocacy partners from the beginning of the study design process. Clinical impacts are expected to span multiple aspects of care, impacting researchers, clinicians, and patients. In terms of research, the development of digital clinical end points will enhance the rigor of clinical trials for the development of improved therapeutics. For clinicians, a longitudinal, real-time assessment of the pain experience will introduce opportunities for individually tailored treatments. Finally, this study is an important step toward promoting patient empowerment through opportunities for proactive self-management and enhanced self-efficacy in living with chronic pain.

## Appendix

Multimedia Appendix 1 Link to 30-second sit-to-stand instructional video.

Multimedia Appendix 2 Peer review report report from the ZNS1 SRB-R (22) National Institute of Neurological Disorders and Stroke Special Emphasis Panel HEAL Initiative: Digital Biomarker (National Institutes of Health, USA).

## Abbreviations

30s-STS: 30-second sit-to-stand task
AUPRC: area under the precision-recall curve
AUROC: area under the receiver-operator characteristic curve
HPA: hypothalamic-pituitary-adrenocortical
IRB: institutional review board
MSK: musculoskeletal
NPS: Net Promoter Score
PEG 3-item: Pain, Enjoyment of Life, and General Activity Scale
SHAP: Shapley Additive Explanations
TFA: Theoretical Framework of Acceptability
TRAC-Pain: Targeted Real-time Assessment of Chronic Pain
TSST: Trier Social Stress Test
TSST-OL: Trier Social Stress Test, online/remote
